# Multicentre randomized controlled trial comparing ferric(III)carboxymaltose infusion with oral iron supplementation in the treatment of preoperative anaemia in colorectal cancer patients

**DOI:** 10.1186/s12893-015-0065-6

**Published:** 2015-06-28

**Keywords:** Colorectal cancer, Iron deficiency anaemia, Iron supplementation

## Abstract

**Background:**

At least a third of patients with a colorectal carcinoma who are candidate for surgery, are anaemic preoperatively. Preoperative anaemia is associated with increased morbidity and mortality. In general practice, little attention is paid to these anaemic patients. Some will have oral iron prescribed others not. The waiting period prior to elective colorectal surgery could be used to optimize a patients’ physiological status. The aim of this study is to determine the efficacy of preoperative intravenous iron supplementation in comparison with the standard preoperative oral supplementation in anaemic patients with colorectal cancer.

**Methods/Design:**

In this multicentre randomized controlled trial, patients with an M0-staged colorectal carcinoma who are scheduled for curative resection and with a proven iron deficiency anaemia are eligible for inclusion. Main exclusion criteria are palliative surgery, metastatic disease, neoadjuvant chemoradiotherapy (5 × 5 Gy = no exclusion) and the use of Recombinant Human Erythropoietin within three months before inclusion or a blood transfusion within a month before inclusion. Primary endpoint is the percentage of patients that achieve normalisation of the haemoglobin level between the start of the treatment and the day of admission for surgery. This study is a superiority trial, hypothesizing a greater proportion of patients achieving the primary endpoint in favour of iron infusion compared to oral supplementation. A total of 198 patients will be randomized to either ferric(III)carboxymaltose infusion in the intervention arm or ferrofumarate in the control arm. This study will be performed in ten centres nationwide and one centre in Ireland.

**Discussion:**

This is the first randomized controlled trial to determine the efficacy of preoperative iron supplementation in exclusively anaemic patients with a colorectal carcinoma. Our trial hypotheses a more profound haemoglobin increase with intravenous iron which may contribute to a superior optimisation of the patient’s condition and possibly a decrease in postoperative morbidity.

**Trial registration:**

ClincalTrials.gov: NCT02243735.

## Background

Colorectal carcinoma has a peak incidence in the seventh decade of life and patients often presents with comorbid iron deficiency anaemia. At least a third of patients with a colorectal carcinoma who undergo surgery, are anaemic preoperatively [1].

**Figure 1 Fig1:**
[figure not shown]
Flowchart of FIT-trial

**Figure 2 Fig2:**
[figure not shown]
Study follow-up

Anaemia in patients with colorectal carcinoma is partly caused by gastro-intestinal (GI) blood loss and is partly cancer-related. Cancer related anaemia is multifactorial and is caused by impaired iron absorption, nutritional deficiency and anaemia of chronic disease, which is a cytokine-mediated disorder. These effects cause functional iron deficiency, which is characterized by insufficient available iron at the site of erythroblast production (iron restricted erythropoiesis) with adequate iron stores [2]. In addition, iron is an essential component of a large number of human metabolic enzymes, including ribonucleotide reductase and NADH dehydrogenase [3, 4]. Therefore iron deficiency even without concomitant anaemia is associated with fatigue [5, 6], impaired physical performance and cognitive function [7–9].

Currently there are three options in the treatment of anaemia: blood transfusion, erythropoietin stimulating agents (ESA) and iron supplementation. Blood transfusion and ESA are effective modalities in increasing haemoglobin (HB) levels, however both modalities should be given with caution in oncologic patients as they are associated with an increased risk of cancer recurrence [10, 11] and ESA is even associated with an 17 % increase in overall mortality in oncologic patients [12].

With the application of laparoscopic surgery, blood loss is limited and blood transfusions are rarely necessary. In the LAFA study including 50 % open and 50 % laparoscopic segmental colectomies the blood transfusion rate was only 4 %[1]. This decreasing rate of blood transfusion could be a reason for the moderate attention for the treatment of light to moderate anaemia in the preoperative setting. However it has been shown that preoperative anaemia, even to a mild degree, is independently associated with an increased risk of morbidity and 30-day mortality [12, 13].

There is no standard of care in the treatment of light to moderate anaemia in the preoperative setting; some will have oral iron prescribed others not. A more profound treatment of iron deficiency anaemia could play a crucial role in optimizing patient’s condition prior to surgery [5]. Even tumour response on chemotherapy, as suggested by Lindsey [14], could be negatively influenced by low HB levels [15, 16]. In the Netherlands, average waiting time before surgery in case of a colorectal carcinoma is two to three weeks. This period could be used more effective in the optimisation of patients towards surgery. Studies on iron supplementation (both oral and intravenous) prior to orthopaedic [17] and gynaecologic surgery [18] showed that iron supplementation is effective in treating anaemia, reducing blood transfusions and also reducing length of stay [19].

However, in patients with colorectal carcinoma and concomitant anaemia current evidence on the role of iron supplementation seems inconclusive. This is due to methodological short comings of the studies, with small study populations [20, 21], heterogeneity in iron preparations supplied, the lack of data on surgical outcomes and most importantly due to inclusion of both anaemic and non-anaemic patients [20, 22]. All of the above underlines the need for a new trial on the efficacy of pre-operative iron therapy in treatment of anaemia in patients with a colorectal carcinoma and its effect on outcomes after surgery.

## Methods/design

The aim of this multicentre trial is to investigate which route of iron supplementation is superior in the treatment of iron deficiency anaemia in patients with colorectal carcinoma. By enhancing the preoperative condition of the patient, this trial aims to optimize postoperative outcome in anaemic patients. It is our hypothesis that a more profound approach of anaemia with intravenous iron will lead to a higher percentage of patients with normalization of Hb-level (>12 g/dl (7.5 mmol/l) for women and > 13 g/dl (8 mmol/l) for men) undergoing surgery, which potentially reduces morbidity, length of hospital stay, improves quality of life, decreases fatigue and could be more cost effective compared to current practice with oral substitution of iron.

In addition, an economic evaluation of intravenous iron versus oral iron will be performed. The evaluation will be performed from a societal perspective as (i) a cost-effectiveness analysis with the costs per responder to iron supplementation therapy as primary outcome and (ii) a cost-utility analysis with the costs per quality adjusted life-year (QALY) as primary outcome. The cost effectiveness analysis closely relates to clinical efficacy measure and allows for setting priorities in treatment of anaemia in colorectal cancer patients. The cost-utility analysis allows for a comparison of the societal impact of intravenous iron supplementation on post-operative recovery, such as improved health utility, shorter length of stay and earlier return to daily activities.

### The primary aim of the FIT trial

To compare the percentage of patients with normalization of Hb-level (>12 g/dl (7.5 mmol/l) for women and > 13 g/dl (8 mmol/l) for men) after intravenous versus oral iron therapy in patients undergoing curative surgery for colorectal carcinoma.

Secondary aims of the FIT trial are:2)To analyse the effect of preoperative iron therapy (intravenous versus oral) on postoperative morbidity, length of stay, amount of blood transfusions needed and quality of life and fatigue scores.3)To determine the cost effectiveness of preoperative intravenous iron substitution in comparison with oral substitution.

### Study design

The study is designed as a multicentre randomized clinical trial comparing ferric(III)carboxymaltose infusion with oral supplementation of ferrofumarate in the treatment of preoperative anaemia in colorectal cancer patients. Patients with a proven iron deficiency anaemia who undergo segmental colonic resection or (low) anterior resection because of M0-stage colorectal carcinoma are eligible for inclusion. Patients undergoing local excision of a rectal carcinoma (TEM/EMR/ESR) will not be included. In Fig. 1 you can find the flowchart of the FIT-trial.

When a patient has got a proven iron deficiency anaemia and the patient does not meet the criteria for exclusion, he/she will be included in the trial. Written informed consent will be obtained from each patient. The patients’ albumin and C-reactive protein (CRP) levels are used to derive a Glasgow Prognostic Score (GPS) which can be used as a predictor of post-operative outcome.

Patients will be computer randomized in random blocks of sizes 2 or 4 for either intravenous- or oral iron. Randomization will be stratified for age, colon or rectal carcinoma, open or laparoscopic operation and baseline Hb (8–10 g/dl vs 10–13 g/dl).

Apart from routine 5 year oncological follow-up, patients will be followed more intensively until 6 months after surgery as part of this trial. Hb, transferrin saturation (TSAT), ferritin, Hematocrit and CRP levels are measured at postoperative day 1, day 7, at 4, 8 and 12 weeks to monitor the anaemia.The follow-up schedule is detailed in Fig. 2.

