### Outcome parameters

Our primary endpoint is the percentage of patients with normalization of Hb-level from start treatment until surgery (Hb >12 g/dl (7.5 mmol/L) for women and Hb >13 g/dl (8.0 mmol/L) for men). Our secondary endpoints are morbidity, assessed with the Comprehensive Complication index, amount of blood transfusions needed, length of stay, absolute change in HB from baseline prior to surgery and postoperatively, time needed to achieve normalization of Hb-level, change in baseline of other iron/haematological parameters (TSAT, ferritin, CRP), health-related quality of life and fatigue scores (EQ-5D, EORTC-C30, EORTC -CR29 iMCQ, BFI & iPCQ), relation between anaemia and Glasgow Prognostic Score (derived from CRP and Albumin) and cost-effectiveness of intravenous iron treatment compared to oral. Blood samples to assess Hb- and iron values will be taken at baseline, at admission, postoperative day 1, 7 and after 1-,2- and 3 months.

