### Data-analysis

The intention-to-treat population will include all patients who give their informed consent, for whom there is confirmation of successful allocation of a randomization number, and who received at least one dose of the study medication. Statistical analyses will be performed using SPSS software for Windows version 19.

The primary endpoint, the percentage of patients with a normalised Hb-level at admission will be compared between the two study groups on a intention to treat basis. Using a two-sided Chi-square test at a significance level of 0.05. All data will be collected in an electronic database. The outcome parameters will be analysed with appropriate statistical tests by a statistician blinded for the treatment allocation using the statistical program SPSS software for Windows version 19.

Appropriate summary descriptive statistics will be determined for all secondary endpoints at each visit using raw scores. To assess morbidity the continuous scale of the Comprehensive Complication Index [25] and the categorical Clavien-Dindo classification will be used, for which appropriate statistical tests will be undertaken (the Mann Whitney U test, in case of non-normal distribution, and the Chi squared test respectively). For continuous secondary endpoints, either analysis of variance or analysis of covariance models will be used and where necessary, the repeated measures procedure will be implemented.

Quality of life data (e.g. EORTC-C30, EORTC-CR29 and EQ-5D) will be graphically represented across all time points and analysed using a repeated measures analysis of variance. All tests based on proportions will be analysed using a logistic regression model with treatment as a factor and, where appropriate, other specified covariates to include baseline score. Time-to-event will be analysed with use of Kaplan-Meier Survival analysis and compared using the log-rank test. Where appropriate, a stratified log-rank test and Cox proportional hazard model will be used to explore the potential influences of baseline HB and other specified covariates.

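### The tests named for morbidity take no covariate, although a Glasgow Prognostic Score is already derived; adjusting for it would be a small, nearly free gain on a secondary aim

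*Protocol article*

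**What the plan says.** All references are to the protocol article.

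- **Study design** uses albumin and C-reactive protein to derive a Glasgow Prognostic Score, "which can be used as a predictor of post-operative outcome". The sentence follows consent and precedes the randomisation paragraph. The score is not among the stratification factors, which are age, colon or rectal tumour, open or laparoscopic operation, and baseline Hb band.
- **The primary aim of the FIT trial** opens the secondary aims with morbidity: "To analyse the effect of preoperative iron therapy (intravenous versus oral) on postoperative morbidity".
- **Data-analysis** states that for morbidity "the continuous scale of the Comprehensive Complication Index [25] and the categorical Clavien-Dindo classification will be used", and names "the Mann Whitney U test, in case of non-normal distribution, and the Chi squared test respectively".
- **Data-analysis** then gives two general rules that can carry covariates: "For continuous secondary endpoints, either analysis of variance or analysis of covariance models will be used", and "All tests based on proportions will be analysed using a logistic regression model with treatment as a factor and, where appropriate, other specified covariates".
- **Outcome parameters** gives the score a use of its own, as a secondary endpoint: "relation between anaemia and Glasgow Prognostic Score (derived from CRP and Albumin").

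The score is not named as a covariate in any analysis.

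**The concern.** Morbidity is the first outcome in the secondary aims and a large part of the trial's clinical rationale. The article describes the score as a possible predictor of outcome after surgery, yet the only tests it attaches to morbidity compare two groups and nothing else. If the score predicts complications, a comparison that leaves it out has more unexplained variation than it needs.

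The sample size was set for Hb normalisation alone, and no power is stated for morbidity. Power that costs nothing is therefore worth having there. The stake is limited to efficiency on a secondary outcome. Neither the primary analysis nor the type I error of the morbidity tests is affected.

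**Working it through.** **1. The plan's own figure.** The only sample size given is for the primary endpoint: 45 % against 25 %, two-sided alpha 0.05, power 80 %, chi-square test.

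n = [1.960 × √(2 × 0.35 × 0.65) + 0.842 × √(0.45 × 0.55 + 0.25 × 0.75)]² / 0.20² = 88.1, so 89 per group. Then 89 / 0.9 = 98.9, so 99 per group and 198 in total. This reproduces the plan. The checks below use 89 per arm.

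**2. What adjustment can buy, in general.** If the score explains a share R² of the outcome variance, a linear adjusted analysis multiplies the standard error by √(1 − R²). Start from the difference that has 80 % power unadjusted: (1.960 + 0.842) × √(2/89) = 0.420 SD. Adjusted power is then Φ(2.802/√(1 − R²) − 1.960). R² is assumed, because the document gives none.

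| Assumed R² | Standard error × | Power |
|---|---|---|
| 0.01 | 0.995 | 80.4 % |
| 0.05 | 0.975 | 82.0 % |
| 0.10 | 0.949 | 84.0 % |
| 0.20 | 0.894 | 87.9 % |

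**3. Rank test with and without the score.** Simulation with 89 per arm and a seven-level ordered outcome from a latent logistic model. Assumed inputs: score split 55/25/20 %, and 25 to 40 % of controls with any complication. The comparison is a t test on ranks against the same test with score indicators, which is a rank analysis of covariance. The first run had 6,000 trials per scenario and a repeat had 4,000.

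| Prognostic odds ratio per score point | Gain in power points at treatment odds ratio 0.5 to 0.4 | Repeat |
|---|---|---|
| 1.5 | below 1 | 0.1 to 0.7 |
| 2 | about 2 | 1.5 to 2.8 |
| 3 | 4 to 7 (e.g. 47.9 % to 54.6 %, 69.2 % to 76.3 %) | 4.7 to 7.1 |

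At a treatment odds ratio of 0.75 the gain is at most about 1.5 points (repeat: about 1). With no treatment effect, both analyses rejected in 5.0 to 5.4 % of trials (repeat: 4.6 to 5.7 %). Only the score was adjusted for. The stratification factors and a proportional-odds model were not simulated.

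**4. Which treatment effect is plausible?** The document gives no expected effect on morbidity, but two of its figures allow a rough bound. Take the assumed normalisation rates (45 % and 25 %) and treat the morbidity figures cited in the Discussion (28 % anaemic, 5 % non-anaemic) as fully causal, which is generous.

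- Intravenous: 0.45 × 5 + 0.55 × 28 = 17.65 %
- Oral: 0.25 × 5 + 0.75 × 28 = 22.25 %
- Odds ratio: (0.1765/0.8235) / (0.2225/0.7775) = 0.214/0.286 = 0.75

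That points to the small end of the table.

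**5. Does the general analysis-of-covariance rule already solve it?** Not by itself. In a second simulation, the index had many zeros, the complication risk was halved by treatment, and the score split was 60/25/15 % (all assumed; 3,000 trials per scenario).

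| Control risk by score 0/1/2 | Mann-Whitney | Linear, unadjusted | Linear, score-adjusted |
|---|---|---|---|
| 30/30/30 % | 67 % | 57 % | 57 % |
| 25/35/45 % | 68 % | 58 % | 58 % |
| 20/45/60 % | 72 % | 62 % | 64 % |

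The plain rank test beats the adjusted linear model throughout. The useful change is to adjust the rank analysis, not to swap it for a linear one.

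**The case against.** The case for leaving the text alone is substantial, and most of it stands.

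- **A reader might infer that the plan shuts the score out of the morbidity analysis.** The document does not go that far. Mann-Whitney is conditional on non-normality, the index is called continuous, and the general rules allow analysis of covariance and covariate-adjusted logistic regression. An analysis plan that is not shown may list the covariates. What remains is that morbidity has its own sentence, and the tests named there take no covariate.
- **A reader might infer that the two sections contradict each other.** They do not. The Study design wording is permissive and commits the trial to no adjustment.
- **A reader might infer that the score is collected and then wasted.** It is not, because its relation with anaemia is a listed secondary endpoint. That is a different question from the treatment effect on morbidity.
- **A reader might infer that chance imbalance in the score makes the unadjusted tests misleading.** In a randomised trial the tests remain valid, and their error rate already allows for such imbalance.
- **The size is assumed.** The 4 to 7 points need an odds ratio of 3 per score point, which is 9 from score 0 to score 2, together with a large treatment effect. The document supports neither.
- **Baseline timing is inferred.** The position of the sentence suggests it. The postoperative blood tests listed in Study design include C-reactive protein but not albumin, which fits that reading. No explicit statement is given.

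**Conclusion.** The point holds as an optional improvement of low priority. For morbidity the article names unadjusted tests, while it already derives a score that it regards as potentially prognostic and allows covariate models elsewhere. The tests are valid and nothing has to be withdrawn.

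The likely benefit is small: about 0 to 3 points of power at prognostic odds ratios of 1.5 to 2 per score point, and 4 to 7 points only at 3 with a treatment odds ratio of 0.4 to 0.5. At the treatment odds ratio of about 0.75 suggested by the document's own figures, it is at most about 1.5 points. These figures rest on an assumed score distribution, complication risk and prognostic strength, and on the score being measured before randomisation. If the score hardly predicts complications in these patients, the gain is close to nil.

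**What to change.** In Data-analysis, replace the morbidity sentence by one adjusted comparison for each measure:

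- **Comprehensive Complication Index:** rank analysis of covariance with treatment, baseline Glasgow Prognostic Score (0, 1, 2) and the randomisation stratification factors (age, tumour site, surgical approach, baseline Hb band).
- **Clavien-Dindo:** proportional-odds model with the same terms. This model could also serve for the index.
- **Sensitivity analyses:** the unadjusted Mann-Whitney and chi-square tests as now written.

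In Study design, state that the albumin and C-reactive protein values for the score are taken before randomisation.

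The cost is a few lines of wording. The score is already derived, the methods run in the planned software, and no patient, visit or sample is added. The proportional-odds model brings its own assumption and reports a conditional odds ratio, which the text should acknowledge. The covariates should be fixed before outcome data are seen by arm, because a later choice would be open to challenge.

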### Study procedures

Surgical procedures include all laparoscopic and open segmental resections. Patients randomized to intravenous iron will receive ferric(III)carboxymaltose dosed according to Summary of Product Characteristics (SPC) depending on body weight and Hb-level and it will be administered in one or two infusions with one week in between, prior to the operation. (also see Table 1). The maximum dose administered to the patient may not exceed 15 mg/kg and a maximum of 1000 mg may be administered per week. When the patient has a weight of lower than 35 kg, a dose of 500 mg will be given. Patients randomized to intravenous iron will receive iron infusion on the short stay/colon care unit. Ferric(III) carboxymaltose has to be infused in a period of 15 min. Patients randomized to standard care with ferrofumarate will receive three tablets of 200 mg daily from randomisation until day before surgery. This dose is conform national farmacotherapeutic protocol [23]. When patients remain anaemic postoperatively, they will be supplied with iron according to the allocated study arm.

**Table 1 Tab1:** Determining the cumulative dose of ferric(III)carboxymaltose

Hb mmol/L (g/dl)	Patients weight: 35–70 kg	Patients weight: > 70 kg
<6.2 mmol/L (10 g/dl)	1500 mg	2000 mg
>6.2 mmol/L (10 g/dl)	1000 mg	1500 mg

N.B: The maximum dose administered per week is 1000 mg. The maximum dose administered per patient may not exceed 15 mg/kg. Therefore, for patients with a weight under 67 Kg, all calculated doses should be given in two infusions (as 1000/15 = 66.7)

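### The 15 mg/kg cap should read per infusion, and even so two stated low-weight doses break it: 1500 mg in two infusions under 50 kg, and 500 mg in one under 33.3 kg

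*Protocol article*

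**What the plan says.** All the dosing rules for the intravenous arm are in the protocol article, under Study procedures and in Table 1 with its note.

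- **Cap, main text:** "The maximum dose administered to the patient may not exceed 15 mg/kg and a maximum of 1000 mg may be administered per week".
- **Cap, table note:** "The maximum dose administered per patient may not exceed 15 mg/kg". The weekly limit of 1000 mg is repeated there as a separate rule.
- **Table 1**, titled "Determining the cumulative dose of ferric(III)carboxymaltose": for Hb <10 g/dl, 1500 mg at 35–70 kg and 2000 mg above 70 kg; for Hb >10 g/dl, 1000 mg and 1500 mg respectively.
- **Consequence drawn in the note:** "for patients with a weight under 67 Kg, all calculated doses should be given in two infusions", justified by 1000/15 = 66.7.
- **Number of infusions:** "it will be administered in one or two infusions with one week in between, prior to the operation".
- **Below 35 kg:** a dose of 500 mg, with no mention of splitting it.
- **After surgery:** "When patients remain anaemic postoperatively, they will be supplied with iron according to the allocated study arm".

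Study design stratifies randomisation on "baseline Hb (8–10 g/dl vs 10–13 g/dl", among other factors.

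**The concern.** The weekly limit carries a time unit, but the mg/kg limit is attached to the patient. Read that way, it bounds the total dose, and Table 1, which gives totals, exceeds it over most of its range. A safety limit should not need reinterpreting before it can be used.

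The second problem survives the sensible reading. For light patients with low Hb, the tabulated dose, the cap and the number of infusions cannot all be obeyed. A prescriber who gives the table dose in two infusions exceeds the cap. One who respects the cap and the infusion count gives less preoperative iron than the table assigns. The article announces the sites as follows: "This study will be performed in ten centres nationwide and one centre in Ireland". That makes eleven centres that could settle the matter differently. These patients are eligible: the criteria set no minimum weight, the text doses patients even below 35 kg, and one randomisation stratum is 8–10 g/dl.

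**Working it through.** **Inputs** (all from Study procedures and Table 1): cap 15 mg/kg; 1000 mg per week; at most two infusions a week apart; cumulative doses 1000, 1500 and 2000 mg; 500 mg below 35 kg.

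**1. The article's own figure.** 1000/15 = 66.7 kg, as the note states. The note concludes that lighter patients need two infusions. Splitting helps only if the cap applies to each infusion; a cap on the total would not be relieved by splitting.

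**2. Literal reading (cap on the total).** Minimum weight = dose/15.

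- 1000 mg: 66.7 kg
- 1500 mg: 1500/15 = 100 kg
- 2000 mg: 2000/15 = 133.3 kg

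At 70 kg the total would be limited to 15 × 70 = 1050 mg, so no patient of 35–70 kg could receive the tabulated 1500 mg. At 60 kg the limit is 900 mg against 1000 or 1500 mg in the table; at 80 kg it is 1200 mg against 1500 or 2000 mg.

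**3. Cap per infusion.** Two-infusion maximum = 2 × min(15 × weight, 1000) mg.

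- 1000 mg at 35–70 kg: feasible from 1000/30 = 33.3 kg, so across the whole band.
- 1500 and 2000 mg above 70 kg: two infusions of up to 1000 mg suffice.
- 1500 mg at 35–70 kg: feasible only from 1500/30 = 50 kg.

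However 1500 mg is split in two, one infusion is at least 750 mg. For that cell:

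| Weight (kg) | Two-infusion maximum (mg) | Short of 1500 mg | 750 mg infusion (mg/kg) | Over cap |
|---|---|---|---|---|
| 35 | 1050 | 450 mg (30%) | 21.4 | 43% |
| 40 | 1200 | 300 mg (20%) | 18.8 | 25% |
| 45 | 1350 | 150 mg (10%) | 16.7 | 11% |
| 49 | 1470 | 30 mg (2%) | 15.3 | 2% |
| 50 | 1500 | 0 | 15.0 | none |

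**4. Below 35 kg.** Given at once, 500 mg needs 500/15 = 33.3 kg. At 30 kg the cap is 15 × 30 = 450 mg. Split in two it would fit, but the text does not say whether this fixed dose counts among the calculated doses that the note splits.

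**5. Hb boundary.** Table 1 uses strict inequalities on both rows, so Hb of exactly 6.2 mmol/L (10 g/dl) is in neither. In the stratification, 10 g/dl is an end point of both strata.

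**6. Reach.** The intravenous arm has 198/2 = 99 patients. The article gives no weight distribution, so the number affected cannot be computed.

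**The case against.** The strongest reply has four parts.

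- **The per-patient wording is a slip that the same note resolves.** This stands. A reader might infer from the literal text that most of Table 1 is forbidden, but the document does not support that as its intended rule, because the two-infusion reasoning makes sense only per infusion. The wording still needs correcting.
- **A prohibition outranks a target dose.** Anyone using the note reads the cap just before the two-infusion rule and would probably arrive at 2 × 15 = 30 mg/kg unaided. This largely stands. A reader might infer that the plan directs an overdose of up to 43%. It does not: it states rules that collide, and the lower dose is the likelier outcome. That centres would differ is a possibility, not something the document shows.
- **Dosing is said to follow the product information, and the full protocol is not shown.** Either may settle the low-weight case. That limits any claim that centres have no answer, but it does not reconcile the rules printed in the article.
- **Patients still anaemic after surgery receive more iron.** True, but this comes too late for a primary endpoint measured at admission.

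A reader might also infer a threat to the primary comparison. Nothing supports that. One patient is 1/99, about 1 percentage point, of the intravenous arm, against a planned difference of 45% − 25% = 20 points, and the affected group is probably very small.

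**Conclusion.** The point holds as a minor inconsistency in the dosing rules. The cap is worded per patient where a cap per infusion is meant. With that corrected, the 1500 mg cell cannot be delivered in two infusions from 35 to <50 kg; the gap is 450 mg at 35 kg and closes at 50 kg. The 500 mg dose breaks the cap below 33.3 kg if it is given as one infusion. The other three Table 1 cells are deliverable.

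This rests on the stated limit of two preoperative infusions and on reading the 500 mg as a single infusion. That few patients are affected is a judgement: they must be in the intravenous arm and either weigh 35 to <50 kg with Hb <10 g/dl or weigh under 33.3 kg. The sample size and the primary test are unaffected.

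**What to change.** After the clinical and pharmacy leads have checked the product information:

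1. Replace the cap sentence in the text and in the Table 1 note with: *Each infusion may not exceed 15 mg/kg or 1000 mg, and no more than 1000 mg may be given per week.*
2. Add to Table 1: *At 35 to <50 kg with Hb <6.2 mmol/L (10 g/dl), the preoperative cumulative dose is limited to 30 mg/kg, given in two infusions.* Alternatively, if the leads prefer it and the time to surgery allows, permit a third weekly infusion. Three infusions of 500 mg respect the cap from 33.3 kg, but the third falls two weeks after the first, and the article gives the usual wait as two to three weeks.
3. Below 35 kg, give 500 mg or 15 mg/kg per infusion, whichever is lower.
4. Assign Hb of exactly 6.2 mmol/L (10 g/dl) to one Table 1 row and to one stratum.

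The rule on postoperative iron can stay. The cost is a short dosing clarification sent to the centres. With the 30 mg/kg limit, the downside is less preoperative iron than tabulated: 450 mg at 35 kg, 150 mg at 45 kg, none at 50 kg. With the limit below 35 kg, a 30 kg patient given one infusion receives 50 mg less (500 − 450). The endpoint, sample size and analysis stay as they are.
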